### Sample size

The primary outcome measure will be the proportion of participants who fall during the twelve month follow-up period. Based on the fall rate from similar work in the field we estimate the fall rate in the control arm of this study will be 60%. We further estimate that the intervention will reduce the number of fallers by 33% in this period – a conservative estimate given the 55% reduction in fall rates reported in the UK over 1 year for a study with a similar intervention [37]. Consequently, accounting for dropouts (10%), a power of 90% and a 5% significance level, a total sample size of 234 is required. Based on our previous studies, a sample of 234 will also be adequate for determining clinically significant differences between the groups for our continuously scored measures [38], and for developing multivariate models pertaining to uptake and adherence [39].

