**Methods:**

Community dwelling people aged 65 years or older who are not conveyed to the ED following a fall will be eligible to be visited at home by a research physiotherapist. Consenting participants will receive individualised intervention strategies based on risk factors identified at baseline. All pre-test measures will be assessed prior to randomisation. Post-test measures will be undertaken by a researcher blinded to group allocation 6 months post-baseline. Participants in the intervention group will receive individualised pro-active fall prevention strategies from the clinical researcher to ensure that risk factors are addressed adequately and interventions carried out. The primary outcome measure will be the number of falls recorded by a falls diary over a 12 month period. Secondary outcome measures assessed six months after baseline will include the subsequent use of medical and emergency services and uptake of recommendations. Data will be analysed using the intention-to-treat principle.

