**Follow-up- 12 months**			
Falls (monthly diaries) [33].			**P**
Subsequent use of health services (differentiation between fall-related or other medical reason) collected from monthly diary and with further telephone call for clarification if required.			**S**
GP visit, Specialist medical practitioners visit, ambulance service use, ED presentation, hospital admission, physiotherapy, occupational therapy.			
Number of falls requiring ED attendance and/or hospitalisation collected from monthly diary and with further telephone call for clarification if required.			**S**
Use of NSW Ambulance Service, including time on scene (routinely collected Ambulance Service data).			**S**
Any ED presentation or hospitalisation including Diagnosis Related Group (DRG) and Length of Stay (LOS) data (measured using falls calendar data and corroborated through the NSW Admitted Patient Data Collection).			**S**
Use of any community health services – GP visits, Home medication review (HMR), Aged Care Assessment Team (ACAT) referrals, use of Post Acute Care Service (PACS) services etc. (measured using monthly falls calendar data).			**S**
Uptake and adherence to recommendations (based on initial and post-intervention assessments).	**✗**	✓	**S**

*BA* Baseline Assessment, *RA* Reassessment, *O* Outcome measure, *S* secondary, *P *Primary.

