### Outcome measures

The primary and secondary study outcome measures are listed in Table 1. All participants will be followed for a total of 12 months after the baseline assessment to record the number of falls and use of emergency health care services. The primary outcome measure will be rate of falls over the 12 month follow up period. A fall will be defined as “unintentionally coming to the ground, floor or lower level” [33] and will be recorded on monthly fall calendars which participants will receive after the baseline assessment. Both intervention and control participants will be asked to record the following details regarding falls: number of falls experienced during that month, location of the fall/s (indoor or outdoor fall) and injuries suffered. If calendars are not returned, telephone contact will be made to obtain the relevant information. This method for collection of fall information is recommended as best practice by the Prevention of Falls Network Europe (ProFaNE) [33].

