### Statistical analysis

Analyses will be conducted using SPSS version 20.0 (SPSS Corp, Chicago, Ill, USA) and STATA 12 software (Stata Corp, College Station, Tex., USA). Descriptive statistics will be used to summarise demographic characteristics and baseline data. Proportion of fallers will be compared between groups using the Relative Risk statistic. Fall rates will be compared between groups using Incidence Rate Ratios (IRR) from negative binomial regression models [35]. Between-group comparisons of final EQ-5D (and other continuous measures) will be made using General Linear Models (ANCOVA) controlling for baseline performance and other confounding variables if required. Predictors of adoption and adherence will be analysed using multivariate modelling techniques. An intention-to-treat approach will be used for all between-group analyses.

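### The protocol names two conflicting primary endpoints, the rate of falls and the proportion of fallers, and sizes the trial only for the second without saying which test decides

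*Protocol article*

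**What the plan says.** The primary outcome is described in four places in the protocol article:

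- Abstract, Methods: "The primary outcome measure will be the number of falls recorded by a falls diary over a 12 month period".
- Table 1, 12-month follow-up block: falls from monthly diaries carry the P mark, without saying whether as a count, a rate or a proportion.
- Outcome measures: "The primary outcome measure will be rate of falls over the 12 month follow up period".
- Sample size: "The primary outcome measure will be the proportion of participants who fall during the twelve month follow-up period".

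The Statistical analysis section gives two between-group comparisons of falls, side by side and unranked: "Proportion of fallers will be compared between groups using the Relative Risk statistic", and "Fall rates will be compared between groups using Incidence Rate Ratios (IRR) from negative binomial regression models".

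The Sample size section then states its inputs: "we estimate the fall rate in the control arm of this study will be 60" (percent), and "We further estimate that the intervention will reduce the number of fallers by 33% in this period". It adds 10% dropout, 90% power and a 5% significance level, and arrives at 234 in total. It calls the assumed effect conservative by reference to a 55% reduction in fall rates in a UK study.

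**The concern.** The proportion who fall at least once and the rate of falls are different estimands. A programme that mainly prevents repeat falls can lower the rate clearly and change the proportion little. The two tests therefore have different power and can give different answers in the same data. Three things are at stake:

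- A reader cannot tell which result was pre-specified to decide the trial.
- The stated 90% power belongs to one endpoint, while the outcome section makes the other one primary.
- The comparison that supports the assumed effect sets a reduction in fallers against a reduction in rates, as if the two percentages were interchangeable.

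**Working it through.** **1. Which endpoints conflict.** Everyone is to be followed for 12 months, and one analysis (the negative binomial IRR) serves both the number and the rate of falls. Those two wordings are in effect one count endpoint. The conflict is between that endpoint (Abstract, Outcome measures) and the proportion of fallers (Sample size). Table 1 does not settle it.

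**2. Reproducing 234.** Inputs from Sample size: control proportion 0.60; intervention 0.60 × (1 − 0.33) = 0.402; power 90%; significance 5%; dropout 10%. Assumption: 1:1 allocation, which is not stated. With unpooled variance and a one-sided test:

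n per arm = (1.645 + 1.282)² × (0.60 × 0.40 + 0.402 × 0.598) / (0.60 − 0.402)² = 8.564 × 0.4804 / 0.0392 = 104.9, so 105.

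105 / 0.90 = 116.7, so 117 per arm and 234 in total. The figure is thus a two-proportion calculation; no mean fall rate or dispersion enters it. (It reproduces only with a one-sided 5% test. The two-sided versions tried give 284 to 316 after the same dropout adjustment. The section does not state sidedness, which is a separate matter.)

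**3. Putting the planned effect on the rate scale.** Assume negative binomial counts with mean μ and dispersion k, and an effect that acts through the mean. Then P(no fall) = (1 + kμ)^(−1/k), so μ = ((1 − p)^(−k) − 1)/k for a proportion of fallers p. The documents give no k, so a range is shown. Example at k = 1: control 1/0.40 − 1 = 1.50; intervention 1/0.598 − 1 = 0.672; IRR = 0.672/1.50 = 0.45.

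| Dispersion k | Control mean (60% fall) | IRR equivalent to 40.2% fallers |
|---|---|---|
| 0.5 | 1.16 | 0.50 |
| 1 | 1.50 | 0.45 |
| 2 | 2.62 | 0.34 |

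The UK benchmark is a 55% reduction in rates, i.e. an IRR of 1 − 0.55 = 0.45, the value given in the Background. On a common scale the planned effect is slightly smaller than the benchmark at k = 0.5, about equal at k = 1, and larger at k = 2. Whether it is conservative depends on a dispersion that the protocol does not give.

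**4. What 234 gives for the rate.** With 105 evaluable per arm and a two-sided 5% test, SE(log IRR) = √[(1/μ + 1/(μ·IRR) + 2k)/105], and power = Φ(|log IRR|/SE − 1.96). Example at k = 1, IRR 0.448: SE = √[(0.667 + 1.488 + 2)/105] = 0.199; 0.803/0.199 − 1.96 = 2.08; power 98%.

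| k | Power for the rate if fallers go from 60% to 40.2% | IRR at 90% power | IRR at 80% power |
|---|---|---|---|
| 0.5 | 96% | 0.56 | 0.61 |
| 1 | 98% | 0.53 | 0.59 |
| 2 | 99.7% | 0.49 | 0.54 |

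**5. How far the two tests can differ.** Simulated power at an IRR of 0.45 (105 per arm, 60% control fallers, 3,000 runs per setting), rate against proportion: 99% against 91% at k = 0.5, 98.5% against 81% at k = 1, and 96% against 54% at k = 2.

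**6. If either test could decide.** For two independent 5% tests, 1 − 0.95² = 9.75%. In the same simulation with no effect, at least one test was significant in 8.6%, 8.8%, 10.0% and 9.6% of runs at k = 0.5, 1, 2 and 3. Part of this is the negative binomial Wald test, which rejected in 5.2% to 5.8% on its own.

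**The case against.** The strongest reply is that this is a wording slip with a clear majority reading. The Abstract and Outcome measures agree on a count endpoint, the Table 1 mark is compatible with it, and only the Sample size section departs. It is common to size a falls trial on the proportion for convenience, and an analysis plan may name the primary test. Some of this stands: there are two endpoints and not three, and the rate is the more natural reading. But the Sample size section does not merely use the proportion for planning; it declares it the primary outcome. An analysis plan could choose one endpoint, but the contradiction would remain in the published protocol.

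Two stronger readings are tempting, and the documents do not support them.

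- A reader might infer that the rate analysis is underpowered, by treating the 33% as an IRR of 0.67; power would then be about 64%, 57% and 45% at dispersion 0.5, 1 and 2. The protocol assumes 33% fewer fallers, not a 33% lower rate. Under its own planning effect, 234 is ample for the rate (step 4).
- A reader might infer that the type I error is inflated. No passage says that either test may claim success. The 9–10% arises only if the choice stays open and an unadjusted result on either endpoint is presented as decisive.

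It is also fair to say that keeping the proportion as primary would resolve the contradiction.

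**Conclusion.** The point holds as an internal contradiction: two endpoints are each declared primary, no analysis is designated primary, and 234 with 90% power is derived for only one of them. It should be corrected before unblinding, because until then the confirmatory claim is undefined. The contradiction and the two-proportion origin of 234 rest on the text and its own inputs. The rate-scale figures rest on assumptions that the documents do not give: a negative binomial distribution, 60% control fallers, dispersion 0.5 to 2, 1:1 allocation, 105 evaluable per arm and a two-sided test. They show that the planned effect corresponds to an IRR anywhere from about 0.50 to 0.34, so the claim that it is conservative is not established. They do not show a shortage of power for the rate. The possible type I error of about 9–10% is conditional on how the result is claimed.

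**What to change.** Before unblinding:

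1. Name one primary outcome in the same words in the Abstract, Table 1, Outcome measures and Sample size. The rate of falls over 12 months is the natural choice, since the Abstract and Outcome measures already point to it.
2. In Statistical analysis, label the negative binomial IRR as the primary analysis and the relative risk for the proportion of fallers as secondary.
3. Keep 234 and rewrite the Sample size paragraph as the power for the IRR. State sidedness, and label the control mean and dispersion as assumptions shown over a range. Under the assumptions above, 90% power is reached at an IRR of about 0.56, 0.53 and 0.49, and 80% at about 0.61, 0.59 and 0.54, for dispersion 0.5, 1 and 2. These are illustrations to be replaced if the sponsor has better inputs; no single value should stand alone.
4. Drop the comparison of a 33% cut in fallers with a 55% cut in rates, or make it on one scale. Do not describe an IRR of 0.67 as the planned effect.

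The cost is wording in the protocol and any analysis plan, and an update of the registry entry if it is affected. No extra participants or data are needed.

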### Randomisation

Participants will be randomised after the baseline assessment. Randomisation will be achieved using computer-generated random numbers and randomly permuted block sizes of 4–8. The single centralised randomisation schedule will be undertaken by the NeuRA research studies coordinator with no involvement in the study and group allocation will be concealed from all study investigators and staff using consecutively numbered sealed opaque envelopes.

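### The total of 234 gives the stated 90% power only under a one-sided 5% test that the protocol does not declare; at two-sided 5% the power is about 82–83%

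*Protocol article*

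**What the plan says.** All the design inputs are in the Sample size section of the protocol article.

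- Endpoint used for sizing: "The primary outcome measure will be the proportion of participants who fall during the twelve month follow-up period".
- Control arm: "we estimate the fall rate in the control arm of this study will be 60" per cent.
- Effect: "the intervention will reduce the number of fallers by 33% in this period".
- Error rates: "a power of 90% and a 5% significance level".
- Conclusion: "accounting for dropouts (10%), a power of 90% and a 5% significance level, a total sample size of 234 is required".

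No one-sided or directional test is mentioned there or under Statistical analysis, which plans a relative risk for the proportion of fallers and a negative binomial incidence rate ratio (IRR) for fall rates. No allocation ratio is printed. The Randomisation section gives only "computer-generated random numbers and randomly permuted block sizes of 4–8", so 1:1 is an assumption here.

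**The concern.** A significance level quoted without qualification is normally read as two-sided. On that reading 234 is too small for the power claimed, by more than rounding or a choice of formula can explain. A reader of a null result would then credit the trial with a 10% chance of missing the planned effect when the chance is about 17–18%. If a one-sided 5% test was meant, the trial was sized at the equivalent of two-sided 10%, and nothing in the article tells the reader so.

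**Working it through.** **Inputs.** p1 = 0.60. A 33% relative reduction gives p2 = 0.40 (0.402 if taken as exactly 33%). Power 90%, α = 5%, dropout 10%, total 234, all from the Sample size section. Allocation 1:1 is assumed.

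**Formula** (normal approximation, pooled variance under the null), with p̄ the mean of p1 and p2:

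n per arm = [z_α √(2p̄(1−p̄)) + z_β √(p1(1−p1) + p2(1−p2))]² / (p1 − p2)²

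For 0.60 v 0.40, the first root is √0.50 = 0.7071, the second is √0.48 = 0.6928, and the denominator is 0.04.

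**1. Reproducing the plan's figure: one-sided 5%, 90% power.**
(1.645 × 0.7071 + 1.2816 × 0.6928)² / 0.04 = 105.2, so 106 per arm and 212 evaluable.
- Inflating by 1.1: 233.2, rounded up to 234.
- Dividing the unrounded figure by 0.9: 2 × 105.2 / 0.9 = 233.8.

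With p2 = 0.402 the same formula gives 108 per arm and 238–240 enrolled. The unpooled-variance version gives 105 per arm, and 2 × 117 = 234.

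**2. Two-sided 5%, 90% power.**
(1.96 × 0.7071 + 1.2816 × 0.6928)² / 0.04 = 129.3, so 130 per arm and 260 evaluable. With p2 = 0.402 it is 131.9, so 132 per arm and 264 evaluable.

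| p2 | Evaluable | × 1.1 | ÷ 0.9 |
|---|---|---|---|
| 0.40 | 260 | 286 | 289 (290 for equal arms) |
| 0.402 | 264 | 291 | 294 |

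The stated total is therefore 52 to 60 short (286 − 234 and 294 − 234). Unpooled variance, arcsine, log relative risk and log odds ratio were also tried. No two-sided version at 90% power came below 280 enrolled.

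**3. Power of 234 enrolled.** 234 × 0.9 = 210.6, about 105 per arm evaluable.

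Power = Φ{[(p1 − p2)√n − z_α √(2p̄(1−p̄))] / √(p1(1−p1) + p2(1−p2))}

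Two-sided, p2 = 0.40: (0.20 × 10.247 − 1.386) / 0.6928 = 0.958, and Φ = 83.1%.

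| Evaluable per arm | Test | p2 = 0.40 | p2 = 0.402 |
|---|---|---|---|
| 105 | two-sided 5% | 83.1% | 82.3% |
| 105 | one-sided 5% | 90.0% | 89.4% |
| 117 (no dropout) | two-sided 5% | 86.9% | 86.2% |

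Exact enumeration of the uncorrected chi-square test, two-sided, gives 82.1% and 81.3% at 105 per arm, and 88.2% and 87.6% at 117 per arm. None reaches 90%.

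**4. Effect detectable with 90% power.** At 105 per arm, two-sided, power is 90.7% for p2 = 0.376 and 89.6% for p2 = 0.380. The detectable relative reduction is therefore about 37% (1 − 0.38/0.60 = 36.7%; 1 − 0.376/0.60 = 37.3%), against the 33% planned.

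**The case against.** The best defence is that the article never says two-sided, and that its figure reproduces with a one-sided 5% test. That stands. A reader might infer that the printed total is simply an arithmetic error at the 5% level. The documents do not support this: 105 per arm gives 90.0% power at one-sided 5%.

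Nor do they support the opposite inference, that the sponsor knowingly chose a one-sided test. Nothing declares one. A two-sided 80% calculation on the log relative risk with p2 = 0.402 also lands on the same number (106 per arm, 212 × 1.1 = 233.2, rounded up to 234). The source of 234 cannot be settled from the text.

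It can also be said that sidedness may sit in an analysis plan not shown. Its absence alone would be no finding. The point is that the article prints a specific total as the consequence of specific inputs, and on the ordinary reading of those inputs the total does not follow.

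The harm is also limited. Power of 82–83% is above the commonly used 80%, and neither the type I error nor the effect estimate is affected.

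Finally, a reader might take 82–83% as the power of the trial's primary analysis. The documents do not support that either. The abstract, Table 1 and the Outcome measures section make the number or rate of falls primary, and Statistical analysis compares fall rates by IRR. The figures here describe only the comparison of proportions.

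**Conclusion.** The point holds in conditional form. At the stated 90% power, 234 fits only an undeclared one-sided 5% test. At two-sided 5% the power for 60% v 40% fallers is about 82–83% (81–82% by exact enumeration), so the type II error is about 17–18% instead of 10%. Reaching 90% would take about 286–294 enrolled. This rests on 1:1 allocation (unequal allocation would lower the power), on 10% dropout leaving about 210 evaluable, and on the proportion of fallers as the endpoint. The sentence needs correcting on either reading, because it either overstates the power or omits the test on which it depends.

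**What to change.** In the Sample size section, state whether the 5% is one-sided or two-sided.

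- If two-sided, replace the conclusion with: *a total of 234 (about 210 evaluable after 10% dropout) gives about 82–83% power at two-sided 5% to detect 60% versus 40% fallers.*
- If one-sided 5% was intended, declare it, give the reason, and carry it through to the Statistical analysis section.

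In both cases add that this power is for the proportion of fallers and not for the fall-rate IRR.

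The cost is a sentence or two and, in the two-sided case, a less favourable stated power. Correcting the text needs no extra recruitment. Only a sponsor wishing to keep 90% power at two-sided 5% would have to raise the total to about 286–294.

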## Discussion

A lack of evidence regarding the effectiveness or feasibility of alternate models of care following ambulance non-conveyance of older fallers, has resulted in a need to explore assessment and intervention programs to help reduce subsequent falls, related injuries and subsequent use of health care services. Previous studies conducted in the ED with patients presenting with a fall have demonstrated benefits of a multifactorial approach to intervention in terms of reducing falls [40] and the risk of functional impairment [41]. Recent evidence from the UK specifically addressing interventions offered to non-conveyed fallers also supports this multidisciplinary approach and demonstrated a significant reduction in falls and a positive effect on patient health outcomes as a result of the intervention [17].

This study is putting in place an approach to intervention that is being tested in a different health system in a different part of the world and where possible is using a service linking approach with existing services rather than setting up a new team. The approach is consistent with National Guidelines [18]. By linking existing services rather than setting up new services, this pragmatic trial aims to utilise the existing health care system infrastructure in an efficient and timely manner and has the potential benefit of being both generalizable and sustainable.

The feasibility of the project is contingent on a number of factors including paramedic referral of eligible participants, participants’ willingness to enrol into the study, GPs to provide necessary referrals and participant adherence to the intervention recommendations. A number of strategies will be employed to engage with the paramedics so as to optimise recruitment including regular station meetings, electronic communication and feedback on the types of intervention being offered to participants they have referred. Telephone communication will be used for GPs when seeking referrals to various parts of the healthcare system. Lastly, by staying in regular contact with all participants and providing timely and ongoing support we hope to achieve high adherence rates. Adherence to a home-based exercise program has been shown to be higher compared to group-based exercise programs among older people [42]. Adherence will also be maximised by using written descriptions [43], training diaries [44] and continued support through telephone contact from the exercise instructor [45], in accordance with the Otago Exercise Programme protocol.

The design of the study is such that, if effective, it would be relatively easy to embed into normal practice as the approach used is focusing on processes to link existing services rather than creating new services.

